**Sampling Framework**

***Schools:***

There are total 188 schools in Chandigarh, of which 115 are government and 73 are private. Twenty-four schools (double than the required number of twelve schools) will be randomly selected from the list of 115 public schools functioning in Chandigarh city. Administrators of these 24 schools will be approached from the list sequentially for obtaining their consent. After receiving consent from the first twelve schools, the list will be closed. From within the 12 selected schools, 12 clusters will be selected randomly using the following procedure.

***Adolescents***

A number will be assigned on folded paper slips for all the sections of the 8^th^ grade. Later, a slip will be randomly selected from the shuffled lot by a person other than the researcher. The section numbered in the slip will be then be selected as the cluster for the study. The above-mentioned method will be applied to select a section of 8^th^ grade in each of the selected twelve schools. Adolescents studying in 8^th^ grade are between 10-16 years of age. All students from class who give the consent to be part of the research study will be involved in the study.

***Parents & teachers***

Parents (or guardians) & teachers (class teacher, subject teachers, physical education teacher, counselor, mid-day meal in-charge (wherever, applicable) and medical in charge) will be involved in the research study, only the parents (or guardians) and teachers who give consent will be part of research study. Either mother or the father of the child will be involved in the research study based on their time availability.

**Intervention Development**

Interventions will focus on following risk factors leading to chronic diseases:

- Poor dietary habits
- High salt intake
- High sugar intake
- Eating junk and fast food
- Overeating
- Physical inactivity
- Sitting for long hours
- Very less walking and no form of exercise
- Tobacco smoking & chewing
- Alcohol

As the major reasons for the most of the chronic diseases are poor diet and physical inactivity. It is important to understand what social, environmental and behavioral factors affect the diet and physical activity and also what other factors such as tobacco & alcohol may lead to or contribute to risk factors of various chronic diseases.

**Methods for Objective 1**

Quantitative data will be used to identify behavioral risk factors.

A baseline survey will be carried out where, demographic details of each participant such as name, age, sex, education, occupation, number of family members, annual income, and knowledge and practices about the risk factors of chronic diseases will be collected from students, parents and teachers. Anthropometric measurements, such as, height and weight, BMI, waist circumference, hip circumference, waist-hip ratio, skin-folds (triceps and sub-scapular), mid- upper arm circumference and maximum hand grip strength will be taken before and after intervention. This will be one of the parameter to assess the effectiveness of the intervention. Hypertension will be checked for students, parents and teachers in pre & post intervention in both intervention and control arm.

**Prevalence will be measured for different set of audience as presented below:**

| **Measurements (Physiological)** | **Audience** |
| --- | --- |
| Blood Pressure | Students, their parents & teachers |
| **Measurements (Anthropometric)** | **Audience** |
| 1. Height 2. Weight 3. BMI 4. Waist circumference 5. Hip circumference 6. Waist-Hip Ratio 7. Mid upper arm circumference 8. Skin-folds  A) Triceps  B) Sub-scapular 9. Maximum hand grip strength | Students, their parents & teachers |
| **Measurements (Biochemical)** | **Audience** |
| 1. Fasting blood samples (plasma glucose levels and lipid levels) 2. 24-hour and spot urine samples (24-hour excretory sodium levels) | Students, their parents & teachers |

**Procedure for measurements**

**Anthropometric measurements**

1. Height
   Make the participant stand straight on the floor board of the stadiometer with his or her back to the vertical backboard of the stadiometer. The weight of the participant should be evenly distributed on both the feet. The heels of the feet should be placed together with both heels touching the base of the vertical board. The feet should be pointed slightly outward at a 60 -degree angle (see Exhibit 3-1). If the participant has knock knees, the feet should be separated so that the inside of the knees are in contact but not overlapping. The buttocks, scapulae, and head are positioned in contact with the vertical backboard. It may not be possible for some children and most adults to place their heels, buttocks, scapulae and the posterior aspect of the head against the backboard while maintaining normal stature. Such participants should be positioned so that only the heels and buttocks are in contact with the vertical board, and the body is positioned vertically above the waist. The arms should hang freely by the sides of the trunk with palms facing the thighs. The participant should be asked to inhale deeply and to stand fully erect without altering the position of the heels. The participant’s head should be maintained in the Frankfort Horizontal Plane position while the examiner lowers the horizontal bar snugly to the crown of the head with sufficient pressure to compress the hair. Hair ornaments, buns, braids, etc. must be removed to obtain an accurate measurement. The bar is locked in place and measurement to be recorded by the recorder to the nearest 0.1 cm.
2. Weight

Participant is asked to remove their heavy outer garments (jacket, coat, throusers, skirts, etc.) and shoes. If participant refuse to remove trousers or skirt, at least make them empty their pockets and record the fact in the data collection form. The participant stands in the centre of the platform, weight distributed evenly to both feet. Standing off-centre may affect measurement. The weight is recorded to the resolution of the scale (the nearest 0.1 kg or 0.2 kg).

1. Waist circumference

When participant is in is in a standing position. The examiner stands behind the participant and palpates the hip area for the right iliac crest (see Exhibit 3-6). The examiner marks a horizontal line at the high point of the iliac crest and then crosses the line to indicate the midaxillary line of the body. The pants and underclothing of the participant must be lowered slightly for the examiner to palpate directly on the hip area for the iliac crest. The examiner then stands on the participant’s right side and places the measuring tape around the trunk in a horizontal plane at this level marked on the right side of the trunk. The recorder walks around the participant to make sure that the tape is parallel to the floor and that the tape is snug, but does not compress the skin. The measurement is made at minimal respiration to the

nearest 0.1 cm.

1. Hip circumference

The participant should be standing erect with feet together and weight evenly distributed on both feet. The examiner squats on the right side of the participant and places the measuring tape around the buttocks. The tape is placed at the maximum extension of the buttocks . The recorder then adjusts the sides of the tape and checks the front and sides so that the plane of the tape is horizontal. The zero end of the tape is held under the measurement value. The tape is held snug but not tight.

1. Triceps skinfold

The participant should be standing erect with feet together, shoulders relaxed and the arms hanging freely at the sides. The examiner stands behind the participants’s right side. The point on the posterior surface of the right upper arm is located in the same area as the marked midpoint for the upper arm circumference. A fold of skin and subcutaneous adipose tissue is grasped gently with thumb and fingers approximately 2.0 cm above the marked level with the skinfold parallel to the long axis of the arm. The jaws of the calipers are placed at the marked level, perpendicular to the length of the fold, and the skinfold thickness is measured to the nearest 0.1 mm while the fingers continue to hold the skinfold.

1. Subscapular skinfold thickness

The participant should be standing erect with shoulders and arms relaxed at the side. The examiner palpates for the inferior angle (or triangle portion) of the right scapula. The examiner makes a (+) on the inferior angle of the scapula with the cosmetic pencil marker. The examiner grasps a fold of skin and subcutaneous adipose tissue directly below (1.0 cm) and medial to the inferior angle. The skinfold forms a line about 45 degrees below the horizontal extending diagonally toward the

right elbow. The jaws of the caliper are placed perpendicular to the length of the fold about 2.0 cm lateral to the fingers with the top jaw of the caliper on the mark over the inferior angle of the scapula. The skinfold thickness is measured to the nearest 0.1 mm while the fingers continue to hold the skinfold.

1. Mid-upper arm circumference

Wrap the measuring tape around the arm at the level of the upper arm mid-point mark. Position the tape perpendicular to the long axis of the upper arm. Pull the two ends of the overlapping tape together so that the zero end sits below the measurement value and the result lies on the lateral aspect of the arm (not the posterior surface). Check that the tape fits snug around the arm but does not compress the skin. Take the measurement to the nearest 0.1 cm.

1. Maximum hand grip strength

Ask the participant to squeeze the dynamometer with as much force as possible, being careful to squeeze only once for each measurement. Three trials should be made with a pause of about 10-20 seconds between each trial to avoid the effects of muscle fatigue. Record the result of each trial to the nearest pound or kilogram. If the difference in scores is within 3 kgs., the test is complete. If the difference between any two measures is more than 6.6 lbs. or 3 kgs., then repeat the test once more after a rest period. Use the best 3 measurements (ie. the highest three) in your data report.

**Physiological measurements**

Blood pressure

Insert the air plug into the air jack. The instrument should be on a level with the heart of the participant. Put the participant’s arm through the cuff loops. Position the arm correctly – The bottom edge of the cuff should be 1 or 2 cm above the elbow. Marker (arrow under tube) is centered on the middle of inner arm. Close the Velcro fastener when the cuff snugly encircles upper arm. Press the START / STOP button. Note down the reading of systolic, diastolic pressure, pulse rate Take the reading again five minutes later and note the readings and remove cuff. Take the average of three BP readings to get the BP of the individual

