**Study Design**

Study design is Cluster Randomized Controlled Trial. Each school will be one cluster.

Schools will be randomized to intervention and control group and net changes in the knowledge and practices related to chronic disease risk factors among students, their parents and teachers will be computed by measurements before starting the health promotion intervention and after implementation of the intervention in both intervention and control clusters.

Research approach will be mixed methods: It will have both qualitative & quantitative data. Quantitative data will be collected using validated tools. Qualitative data will be collected by carrying 10 focused group discussions with students, their parents and teachers separately to understand their perception about risk factors and lifestyle behaviors (2 with male teachers, 2 with female teachers, 2 with female students, 2 with male students and 2 with parents in government schools).

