|  | *Primary audience:* Adolescents of the randomly selected clusters (sections of 8^th^ grade)  *Secondary audience:* Parents & teachers of adolescents | - Vendors outside school premises - Unhealthy food options in the school canteens - Study load (tuitions after school hours & homework) - Stringent school time-table | - To catch adolescents before risky behaviours start developing - Using schools as a platform for promoting healthy behaviours | Educational classes and classroom discussions | Researcher | 30 minutes session every fortnight | Verbal (2-way communication) &  Digital audio-  visual method (PowerPoint presentation using the laptop) |
|  |  |  |  | Physical activity sessions | Researcher/ physical education teachers | Four sessions every week with each session of 30 minutes | Verbal (2-way communication) |
|  |  |  |  | Other interactive activities: Poster making competition & grow your own herbs | Researcher | Two sessions during intervention period with each session of about 45 minutes | Verbal (2-way communication) |
|  |  |  |  | Peer-to-peer education for reduction in the use of tobacco and alcohol | Researcher | One session every month with each session of 15 minutes | Verbal (2-way communication) |

**Behavior Change Communication Matrix- Intervention fr promoting recommended level of salt, sugar, fruits and vegetable intake along with increase in physical activity and reduction in use of tobacco and alcohol in public schools of Chandigarh**

Purpose of the Intervention: To promote positive changes in attitudes and behavior related to salt, sugar, fruits and vegetable intake, increase in physical activity and reduction in use of tobacco and alcohol among adolescents, their parents & teachers.

| **S.No** | **Risk Factors** | **Goal** | **Activities** |
| --- | --- | --- | --- |

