**Methods for Objective 3:**

Effectiveness of the intervention will be measured using following indicators in the baseline and end line sample survey among adolescents:

Before the intervention, perceptions, knowledge and practice of case and control group adolescents will be assessed for the chronic diseases and their risk factors with the help of a questionnaire. This will help in measuring the extent of behavior change. This questionnaire will be used as one parameter to assess the effectiveness of the intervention as the same questionnaire will be used after the completion of the intervention. This will help in assessing the improvement of the perception, knowledge and practices.

For objective measurements, anthropometric measurements, such as, height and weight, along with physiological measurement (blood pressure), biochemical measurement (24-hour excretory sodium through spot urine samples) will be taken before and after intervention. This will be the second parameter to assess the effectiveness of the intervention. The net changes in primary and secondary outcome measures among parents and teachers will be considered as exploratory analysis,

| **Intervention** | **Impact** | |
| --- | --- | --- |
|  | **Direct** | **Indirect** |
| Diet | Participant | Family |
| Physical activity | Participant | Family |
| Alcohol | Participant | Family |
| Smoking | Participant | Family |

**Table:** Impact of different interventions on the participants and their families.

| **Expected outcome of Intervention** |
| --- |
| 1. Increase in knowledge about various chronic diseases and their risk factors 2. Positive response for behavior for diet and physical activity 3. Increase in normal BMI and waist-hip ratio 4. Reduction in risk factors of chronic diseases, such as, decrease in salt and sugar intake and increase in iron intake. 5. Reduction in the consumption of junk food. 6. Adherences to the medicine among those having chronic diseases. 7. Change in stage of behavior |

**Table:** Expected outcomes of intervention package

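### The blood pressure procedure states no rest before the first reading and keeps that reading in the average, so recorded blood pressure and the baseline prevalence of raised blood pressure are liable to be overstated

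*Protocol*

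**What the plan says.** The blood pressure steps are under Physiological measurements in the Protocol. Once the cuff is positioned, the instruction is "Close the Velcro fastener when the cuff snugly encircles upper arm. Press the START / STOP button". The values are noted, and then: "Take the reading again five minutes later and note the readings and remove cuff". The closing rule is "Take the average of three BP readings to get the BP of the individual".

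Two readings are described and three are averaged, so the text conflicts with itself on the number. Whatever the number, no rest is stated before the first reading and none is excluded from the mean. No other section adds either step.

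Blood pressure has two uses:

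- **Prevalence (Objective 1).** Methods for Objective 1 states "Hypertension will be checked for students, parents and teachers in pre & post intervention in both intervention and control arm".
- **Effect (Objective 3).** Among adolescents, Methods for Objective 3 lists anthropometry "along with physiological measurement (blood pressure), biochemical measurement (24-hour excretory sodium through spot urine samples) will be taken before and after intervention". Study Design defines the effect as a net change, obtained "by measurements before starting the health promotion intervention and after implementation of the intervention in both intervention and control clusters".

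Between the two surveys, the table in the Detailed intervention plan makes the researcher responsible for the adolescents' classes ("30 minutes session every fortnight"), for monthly peer education and for the interactive activities. Responsibility for four physical activity sessions a week is shared with the physical education teachers. No contact with control pupils between surveys is described.

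**The concern.** A reading taken as soon as the cuff is closed is the one most open to an alerting response to the device and the observer. The procedure already contains a five-minute interval, but places it where it cannot protect that reading.

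Two results could be affected. A prevalence estimate has no comparator, so any upward shift passes straight into the baseline proportion with raised blood pressure in pupils, parents and teachers. A before-after fall within one arm is also unprotected if people are less alert at the second survey.

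This is not a level of detail that the Protocol otherwise leaves open. It fixes posture for height, waist, hip and skinfolds. For grip strength it sets the pauses, the repeat rule and which trials count. Blood pressure gets an averaging rule but no rest.

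**Working it through.** The Protocol gives no blood pressure SD, cut-off, target effect or sample size, so there is no figure of its own to reproduce. The check is bias arithmetic on stated assumptions.

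**Inputs from the Protocol**
- Readings averaged: n = 3 by the averaging rule, or n = 2 if only the readings described are taken.
- First reading included, with no stated rest before it.
- Effect measure: change in intervention clusters against change in control clusters.

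**Inputs assumed (not in the documents)**
- Excess of the first reading over the settled value: e = 3 to 8 mmHg, confined to that reading.
- Between-person SD: 10 mmHg, normal distribution.
- True proportion above a cut-off: 5% or 10%.

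**Step 1: inflation of the recorded mean = e / n**
- n = 3: 3/3 = 1.0 mmHg; 8/3 = 2.67 mmHg.
- n = 2: 3/2 = 1.5 mmHg; 8/2 = 4.0 mmHg.

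**Step 2: reported proportion = 1 − Φ(z − inflation/10), for n = 3**
- True 5% (z = 1.645): 1 − Φ(1.545) = 6.1%; 1 − Φ(1.378) = 8.4%.
- True 10% (z = 1.2816): 1 − Φ(1.182) = 11.9%; 1 − Φ(1.015) = 15.5%.

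**Step 3: bias in the between-arm net change = −e × (h_int − h_ctl) / n**

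Here h is the fraction of the first-reading excess that has gone by end line in each arm. With e = 8 and n = 3:

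| h, intervention | h, control | Bias (mmHg) |
| --- | --- | --- |
| 0.5 | 0.5 | 0 |
| 0.5 | 0.25 | −0.67 |
| 1 | 0.5 | −1.33 |
| 1 | 0 | −2.67 |

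Equal habituation gives zero whatever the value of e. A gap of 0.5 between the arms gives −0.5 mmHg at e = 3 (3 × 0.5/3) and −1.33 mmHg at e = 8. The last row is an extreme: it needs complete habituation in one arm and none in the other.

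**Step 4: price of excluding the first reading**

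If readings vary independently within a person, averaging two instead of three raises the within-person standard error by √(3/2) = 1.22. That applies to the within-person part only, not to the differences between people.

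**The case against.** The strongest reply is that the error comes from outside the documents. Nothing in them shows that first readings run high, by how much, or that five minutes settles them. An unstated rest does not prove that none is given, and averaging every reading is a recognisable choice. All of that stands. It is why the point is that blood pressure is liable to be overstated. A reader might infer that raised blood pressure is overstated as a fact, and the documents do not support that.

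A reader might also infer that intervention pupils, used to the research team after six months, will show a spurious fall relative to controls. The documents do not support that either:

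- The same procedure applies in both arms at both surveys, so shared habituation cancels in the net change.
- Control pupils are also measured at baseline, so the device and procedure are new to neither arm at end line.
- The procedure does not say who takes blood pressure. The researcher is named for the teaching sessions, not for this measurement.

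Extra habituation in the intervention arm is possible, for instance if the same researcher also measures, but that is a condition and not a finding.

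Three further points stand. Blood pressure is in neither the hypotheses nor the sample-size table, and changes in parents and teachers are exploratory. If the alerting response extends past the first reading, excluding that one reading is only a partial cure. With the two readings actually described, excluding the first leaves a single value, so the exclusion depends on settling the number of readings.

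What the reply does not remove is that staff who follow the procedure as written will take the first reading without a rest and average it in. Nothing obliges them to give a rest, or the same rest at both surveys.

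**Conclusion.** The point holds as a modest weakness in a measurement procedure. As written, the least settled reading enters both an Objective 1 prevalence measure and an Objective 3 effect measure.

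If the first reading is 3 to 8 mmHg too high, the three-reading mean is inflated by 1.0 to 2.7 mmHg. With an SD of 10 mmHg, a true 5% above a cut-off then reads as 6.1% to 8.4%. The excess, the SD and the true proportion are all assumptions, so these figures show sensitivity and do not estimate what will happen in this trial.

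The exposure lies mainly in the baseline prevalence and in any before-after change read within one arm. For the between-arm net change the expected bias is zero under equal habituation. It favours the intervention only if intervention pupils habituate more than controls, which the documents leave open. The change is worth making because it is cheap and the paragraph has to be revised anyway. It does not put the trial's main comparisons in doubt.

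**What to change.** Rewrite the blood pressure paragraph in the same edit that reconciles the number of readings:

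- Place a quiet seated period with the cuff on before the first reading. The five-minute interval already in the procedure would serve.
- Describe all three readings, with their timing.
- Record the first reading, but define the individual's blood pressure as the mean of the later two.
- State that this applies identically in both arms, at baseline and at end line.

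The three readings must be described before the first is excluded from the mean. The cost is a few lines of text, about five minutes per person, and slightly more random error from one fewer averaged reading. Because the first reading is still recorded, its excess over the later two can be reported by arm and survey, which would replace the assumptions used here with data.
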